### Subpopulation analysis

A subpopulation of patients with serum potassium levels greater than or equal to 5.0 mmol/L or less than 5 mmol/L at the time of patient enrollment and low or high awareness of potassium restriction will be generated, and each subpopulation will be analyzed at 3.5.2.

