## Methods of statistical analysis

### Population to be analyzed

The main analysis of the primary endpoint and secondary endpoint is the one targeting the Full Analysis Set. In addition, we will also conduct an analysis of the Per Protocol Set to confirm the stability of the analysis results.

(1) Definition of Full Analysis Set

Cases that meet all of the following criteria are considered to be cases.

(1) eGFR less than 45 ml/min/1.73 m2 and serum potassium level of 4.0 mmol/L or more

(2) Patients who have obtained consent for this study at an insurance pharmacy

(2) Definition of Per Protocol Set

　　Patients with FAS who meet all of the following criteria are considered to be FAS.

(1) Patients who obtained the results of questionnaire 2 after 84 days after obtaining consent

(2) Patients with resting blood pressure after visiting the clinic after 84 days after obtaining consent

(3) Patients who responded to a questionnaire about their awareness of potassium restriction after the intervention

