### Statistical analysis

(1) Primary endpoint

The mean and standard deviation of serum potassium levels before and after the intervention will be calculated, and a paired student's t-test will be performed at 5% on both sides of the significance level.

(2) Secondary endpoint

The mean and standard deviation of resting blood pressure before and after the intervention will be calculated, and a student's t-test will be performed with a significance level of 5% on both sides. For the content of the questionnaire, Fisher's exact test or chi-square test will be performed at a significance level of 5% on both sides of the change in awareness of potassium limitation.

(3) Comparison of patient backgrounds

Nutritional guidance will be used to compare the patient's background between the improved and non-improving serum potassium groups. For the nominal variables of gender, medical history, medication administration at home, and eating at home, Fisher's exact test or chi-square test is performed at 5% on both sides of the significance level. For the continuous variables age, Body mass index, and eGFR, the mean and standard deviation are calculated, and a student's t-test is performed with a correspondence of 5% on both sides of the significance level.

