## Observation items and methods

### Observations and information and samples to be collected

The blood and urine test data used in this study will not be newly tested because the data obtained in daily practice will be obtained retrospectively (retrospectively) through electronic medical records.

(Pre-intervention)

- Patient background: age, gender, body mass index, medical history (heart failure, diabetes), how to manage medications at home (family management or self-management), meals at home (self-catering, home delivery, eating out)
- Blood tests: serum albumin level, Na, Cl, K, Mg, aspartate aminotransferase, alanine aminotransferase, eGFR, blood urea nitrogen, red blood cell count, white blood cell count, Hemoglobin level, hematocrit, platelet count
- Urinalysis: urine albumin, urine albumin/creatinine ratio, or urine protein, urine protein/creatinine ratio
- Oral medications: presence or absence of concomitant medications (mineralocorticoid receptor antagonists, renin-angiotensin-aldosterone inhibitors, sodium glucose cotransporter2 inhibitors) that increase serum potassium levels, presence or absence of concomitant medications (loop diuretics) that reduce serum potassium levels, presence or absence of potassium adsorbents
- Vitals: Resting blood pressure (systolic and diastolic) after visiting the station

In addition, if the blood pressure at home is recorded in the blood pressure notebook, it is possible to substitute the resting blood pressure after the visit.

(12 weeks after intervention)

- Patient background: age, gender, body mass index, medical history (heart failure, diabetes), how to manage medications at home (family management or self-management), meals at home (self-catering, home delivery, eating out)
- Blood tests: serum albumin level, Na, Cl, K, Mg, aspartate aminotransferase, alanine aminotransferase, eGFR, blood urea nitrogen, red blood cell count, white blood cell count, Hemoglobin level, hematocrit, platelet count
- Urinalysis: urine albumin, urine albumin/creatinine ratio, urine protein, urine protein/creatinine ratio
- Oral medications: presence or absence of concomitant medications (mineralocorticoid receptor antagonists, renin-angiotensin-aldosterone inhibitors, sodium glucose cotransporter2 inhibitors) that increase serum potassium levels, presence or absence of concomitant medications (loop diuretics) that reduce serum potassium levels, presence or absence of potassium adsorbents

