### Exclusion Criteria

1. Patients who do not agree to participate in this study
2. Patients who have difficulty communicating
3. Patients with hypokalemia (serum potassium level less than 4.0 mmol/L)
4. Patients undergoing maintenance dialysis
5. Patients Bringing Refill Prescriptions
6. Patients taking potassium preparations internally
7. Patients who are not expected to continue to visit the insurance pharmacy in the study for more than 3 months

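### One routine potassium value appears to serve as eligibility value, subgroup value and baseline, so regression to the mean will look like an effect, mainly in the subgroup at or above 5.0 mmol/L

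*Protocol*

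**What the plan says.** - **Design** (Protocol, opening schema and Section 0.1): single-arm, open, before-and-after comparison with no control.
- **Selection** (Sections 4.1.2 and 3.5.1): patients with potassium below 4.0 mmol/L are excluded, and the Full Analysis Set requires "eGFR less than 45 ml/min/1.73 m2 and serum potassium level of 4.0 mmol/L or more".
- **Primary test** (Section 3.5.2): the mean and SD of "serum potassium levels before and after the intervention will be calculated, and a paired student's t-test will be performed", two-sided at 5%.
- **Subgroups** (Section 3.5.3): one split is into "patients with serum potassium levels greater than or equal to 5.0 mmol/L or less than 5 mmol/L at the time of patient enrollment", and "each subpopulation will be analyzed at 3.5.2". For the primary endpoint that means the paired t-test within each subgroup.
- **Source of the values** (Section 3.6.1): blood and urine data "will not be newly tested because the data obtained in daily practice will be obtained retrospectively" from the electronic record. The schedule in Section 3.6.2 checks blood data at Day 1 and from Day 84 onwards, and at no other time.
- **Interpretation** (Section 8.2): a fall in potassium over three months is expected as a benefit of the guidance.

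The protocol does not mention regression to the mean or plan a second pre-intervention value.

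**The concern.** A single potassium reading combines the patient's usual level with short-term variation and measurement error. Patients picked because one reading lies above a cut-off have, on average, positive short-term deviations in that reading. At the next reading those deviations are gone and the mean falls. If the picking value is also the baseline, this fall enters the paired difference, and without a control group nothing in the design subtracts it.

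The cut at 4.0 lies below any plausible mean for these patients and removes only a lower tail, so it does little. The cut at 5.0 selects an upper tail and does a lot. Below 5.0 the artefact is near zero or upward. Separate tests in the two subgroups could therefore show a significant fall in one and none in the other with no effect at all, and invite the conclusion that guidance works in patients with high potassium. The protocol itself fixes the cut, the test and the data points, so this is not detail left to an analysis plan.

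**Working it through.** **1. The plan's own figure.** Section 3.2.2 gives n = 34 for a mean difference of 0.5 mmol/L and SD 1.0. Exact paired-t power, two-sided 5%, is 0.795 at n = 33 and 0.808 at n = 34, so 34 reproduces. (The section prints α = 0.8 and β = 0.05; the result follows only with α = 0.05 and power 0.8.)

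**2. Are the three values one draw?** The protocol does not say so in words. It orders no new test and schedules one blood check before the intervention and one from Day 84 onwards. No other pre-intervention potassium is available for eligibility, grouping and baseline, so this is a clear inference.

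**3. Expected change with zero effect.** For normally distributed potassium with mean μ, SD σ and correlation ρ between the two readings, selection on baseline ≥ c gives

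expected change = −(1 − ρ) · σ · h(z), with z = (c − μ)/σ and h(z) = φ(z)/(1 − Φ(z)).

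From the protocol: c = 4.0 and 5.0; σ = 0.5 (the reported between-person SD) or 1.0 (the planning SD), both in Section 3.2.2. Assumed, because the protocol does not give them: μ = 4.5 to 4.7 and ρ = 0.5 to 0.8.

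| Group | μ | σ | z | h(z) | Fall, ρ = 0.8 | Fall, ρ = 0.5 |
|---|---|---|---|---|---|---|
| ≥ 5.0 | 4.5 | 0.5 | 1.0 | 1.525 | 0.15 | 0.38 |
| ≥ 5.0 | 4.7 | 0.5 | 0.6 | 1.215 | 0.12 | 0.30 |
| All, ≥ 4.0 | 4.5 | 0.5 | −1.0 | 0.288 | 0.03 | 0.07 |
| All, ≥ 4.0 | 4.7 | 0.5 | −1.4 | 0.163 | 0.02 | 0.04 |
| All, ≥ 4.0 | 4.5 | 1.0 | −0.5 | 0.509 | 0.10 | 0.25 |

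First row at ρ = 0.5: 0.5 × 0.5 × 1.525 = 0.38 mmol/L. For patients from 4.0 to below 5.0 at σ = 0.5, over the wider range μ = 4.4 to 4.8, the expected change runs from −0.04 to +0.11.

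**4. How many patients are at or above 5.0?** At σ = 0.5, the share of eligible patients is 0.159/0.841 = 19% for μ = 4.5 (6.4 of 34, 7.5 of 40) and 0.274/0.919 = 30% for μ = 4.7 (10.1 of 34, 11.9 of 40). Seven and ten are therefore reasonable sizes.

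**5. False significance of the paired t-test, by simulation under zero effect.**

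- ≥ 5.0, σ = 0.5: about 15 to 46% with 7 patients, 21 to 68% with 10.
- Whole sample, n = 34, σ = 0.5: about 5 to 13%.
- Whole sample, n = 34, σ = 1.0, μ = 4.5: about 17 to 34%.

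A repeat with 20,000 trials per scenario gave 15 to 47%, 20 to 67%, 6 to 14% and 15 to 34%. The end-points are good to about two percentage points.

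**6. Does an earlier baseline remove the artefact?** With three equally correlated readings, selecting on the middle one and comparing the last with the first, the mean null change is at most 0.002 mmol/L in size, both for ≥ 4.0 and for ≥ 5.0.

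**7. Would a regression on baseline do instead?** No. In a single arm under zero effect, change still depends on baseline with slope about −(1 − ρ) or steeper. With the earlier value as baseline, σ = 0.5 and n = 34, that dependence is falsely significant in about 54 to 91% of runs.

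**The case against.** Several points against the concern have force.

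- **The primary analysis is barely touched at the reported SD.** A bias of 0.02 to 0.07 mmol/L is small against a target of 0.5. A reader might infer that the main test is badly invalid, with a spurious fall of half the target effect and a type I error near 34%. That needs the planning SD of 1.0 to be the true between-person SD, with correlation 0.5. Section 3.2.2 presents 1.0 as a cautious increase over a reported 0.5, and with mean 4.5 it would put 31% of the source population below 4.0. The protocol states no correlation; 0.5 follows only if that one SD is both the cross-sectional SD and the SD of the differences.
- **A false positive in the subgroup is not shown to be likely.** When the subgroup size is matched to the assumed mean (about 7 patients at mean 4.5, about 10 at mean 4.7), the rate stays below one half. The upper end of 68% pairs mean 4.5 with more high-potassium patients than that mean predicts.
- **The single draw is inferred, not stated.**
- **The study calls itself exploratory** (Section 20), and the worst effect is in a subgroup analysis.

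These points limit the size and weight of the concern. They do not remove it: even the low end, 15%, is three times the nominal 5%, and the direction of the bias for either lower cut-off does not depend on the assumed mean or correlation.

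**Conclusion.** The concern holds for the subgroup at or above 5.0 mmol/L. There a null intervention would show a fall equal to roughly a quarter to three quarters of the planned effect (0.12/0.5 = 24%; 0.38/0.5 = 76%), with an error rate well above 5%. A significant fall in that subgroup, or a contrast with the subgroup below 5.0, could not be read as an effect of guidance.

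For the whole sample the bias has the same direction but is modest at SD 0.5. It becomes material (0.10 to 0.25 mmol/L) only if 1.0 is the real between-person SD.

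The sizes rest on normality, the assumed mean and correlation, and the inference that one value fills all three roles. This should be fixed; on these figures it does not by itself invalidate the primary analysis.

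**What to change.** 1. In Sections 3.5.2 and 3.5.3, use the enrolment potassium only for eligibility and subgroup assignment.
2. Define the baseline as a routine potassium from the same electronic record, drawn before the enrolment value, whatever its level, within a fixed look-back. About 12 weeks earlier is ideal: if correlation decays with time, the bias cancels only when the earlier and the follow-up values are similarly spaced around the enrolment value.
3. Show the analysis with the enrolment value as baseline as a sensitivity analysis.
4. Label the within-subgroup before-after results as descriptive, and state that they are not evidence that guidance works better at high potassium.
5. Do not replace them by a single-arm regression of follow-up or change on baseline; that slope is itself regression to the mean.

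**Cost.** One more value per patient from records already being read, plus wording. Some patients will lack an earlier value; the margin between 40 enrolled and 34 required is 6, and it must also cover dropouts. The baseline is older, and the method assumes that potassium and medication were stable over the look-back. It removes the selection artefact only: other changes over time remain uncontrolled in a single-arm design.

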### Secondary Objectives

| Secondary Objectives | Evaluation items | Reasons and Validity for Selection of Evaluation Items |
| --- | --- | --- |
| Change in Attitudes Toward the Intake of Potassium-Containing Foods | Survey Results | Evaluated on a 5-point scale for questions about awareness of potassium restriction |
| Change in resting blood pressure before and after intervention | Systolic and diastolic blood pressure at rest at visit | Blood pressure fluctuations are expected due to diet |

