# Method and duration of the study

## Study design (research method)

・Case registration

CKD severity classification stages G3b, G4, G53^)^

When the outpatient prescription of the Mie Chuo Medical Center is brought to the insurance pharmacy, the written consent of the patient is obtained and registered. The date of obtaining consent shall be Day 1.

・Intervention method

All of the following interventions are performed by pharmacists at insurance pharmacies.

Date of Obtaining Consent (Day 1)

1. Questionnaire of the Awareness Survey on the Intake of Potassium-Containing Foods in Patients (Questionnaire 1) Appendix 2

2. Dietary guidance: Guidance on nutritional guidance for CKD (Annex 1) will be used. (Recommendation of nutritional guidance to the Nutrition Management Office as necessary)

3. Measurement of resting blood pressure after the visit

4. Provision of information to the Mie Chuo Medical Center on the status of the administration of potassium adsorbents: If the cause of poor adherence is the dosage form or dosage, the information will be provided to the Mie Chuo Medical Center of the prescriber in a tracing report.

⇒ hospital pharmacist writes details such as dosage status on the bulletin board of the electronic medical record to the prescribing physician and proposes a dosage change.

Day1-83

1. Dietary guidance (as appropriate)

2. Measurement of resting blood pressure after the visit

3. Confirmation of the status of potassium adsorbents (if information is provided to Mie Chuo Medical Center, confirmation of dosage type change, etc.)

After Day 84 (end date of the observation period)

1. Questionnaire on the Awareness Survey on the Intake of Potassium-Containing Foods by Patients (Questionnaire 2) Appendix 3

2. Measurement of resting blood pressure after the visit

3. Confirmation of the status of potassium adsorbents (if information is provided to Mie Chuo Medical Center, confirmation of dosage type change, etc.)

Contents of the questionnaire

For all questions, set a five-level answer.

At the time of obtaining consent (Day 1): Questionnaire 1

Q1. Do you know that potassium in the blood should not be too high?

Q2. Do you know of any foods that contain a high amount of potassium?

Q3. Are you conscious of refraining from foods that contain a lot of potassium?

Q4. Is it annoying (troublesome) to be aware of potassium intake?

3 months after obtaining consent (after Day 84): Questionnaire 2

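### Change in awareness is to be tested within subgroups that, on the natural reading, are formed from its own baseline value, so regression to the mean can pass for an effect

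*Protocol*

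**What the plan says.** Section 3.5.3 of the protocol names two splitting variables. The first is potassium: "serum potassium levels greater than or equal to 5.0 mmol/L or less than 5 mmol/L at the time of patient enrollment". The second is awareness: "low or high awareness of potassium restriction will be generated, and each subpopulation will be analyzed at 3.5.2". No endpoint of 3.5.2 is exempted. The sentence gives no item and no cut-off for awareness, and in words it ties the enrolment time point to potassium only.

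Section 3.5.2 (2) prescribes the awareness test: "Fisher's exact test or chi-square test will be performed at a significance level of 5% on both sides of the change in awareness". It does not say whether the five answer levels enter as they are or are collapsed to low and high.

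Awareness is measured twice. Section 3.1 sets "At the time of obtaining consent (Day 1): Questionnaire 1" and repeats Q1 to Q4 in Questionnaire 2 after Day 84. On scale it says "For all questions, set a five-level answer", and section 2.1.2 agrees: "Evaluated on a 5-point scale for questions about awareness of potassium restriction".

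The design summary at the front of the protocol describes an open before-and-after comparison with no control.

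**The concern.** Questionnaire 1 is the only awareness measurement at enrolment. If it forms the subgroups, it also supplies the before half of the change tested inside them. Patients who score low on one imperfectly repeatable answer tend to score nearer the middle on the next, and patients who score high do the same from the other side. Without a control group, nothing in the data shows how much of the movement is of this kind.

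The likely false result is an attractive one: guidance raised awareness in those who lacked it. Change in awareness appears under both the primary objectives (2.1.1) and the secondary objectives (2.1.2). Motivation to follow the diet is the route by which guidance is supposed to act (2.3 and section 5). A spurious subgroup result here would support a wrong conclusion about who benefits.

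**Working it through.** **Inputs from the protocol.** Planned N = 40, from 34 required plus dropouts (3.2.2); two-sided 5% Fisher or chi-square test (3.5.2); five answer levels, with Questionnaire 1 on Day 1 and Questionnaire 2 after Day 84 (3.1); no control group. The protocol gives no figure for the awareness subgroups. Its one computed figure, n = 34, reproduces for a paired t-test with difference 0.5, SD 1.0, two-sided 5% and 80% power (power 0.808 at n = 34). It serves here only as the source of N.

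**Assumptions, not in the protocol.** Guidance has no effect; answers have the same distribution before and after; the latent answers are bivariate normal with retest correlation r; the cut-off and cell structure are as stated in each step.

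**Step 1: how many switches are needed.** With 20 patients low at baseline, the before count of high is 0/20 by construction. For x switches the two-sided Fisher p-value is 2 × C(20,x)/C(40,x).
- x = 4: 2 × 4845/91390 = 0.106
- x = 5: 2 × 15504/658008 = 0.047

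Five switches are enough.

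**Step 2: how many switches chance supplies.** For a median split, the probability of changing sides with no effect is q = arccos(r)/π. The low group rejects with p = P(Bin(20, q) ≥ 5). The high group mirrors it, and at least one rejects with 1 − (1 − p)².

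| r | q | low group | at least one of two |
|---|---|---|---|
| 0.5 | 0.333 | 0.85 | 0.98 |
| 0.7 | 0.253 | 0.60 | 0.84 |
| 0.8 | 0.205 | 0.39 | 0.63 |
| 0.9 | 0.144 | 0.15 | 0.28 |

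Simulation that lets the group sizes vary around 20 gives about 82/56/37/15% for the low group and 98/83/63/27% for at least one.

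**Step 3: other structures** (N = 40, Fisher on low/high, simulated).

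| Structure | r = 0.5 | 0.7 | 0.8 | 0.9 |
|---|---|---|---|---|
| At least one of four potassium-by-awareness cells | 70% | 37% | 19% | 5% |
| One low-awareness cell of those four | 24% | 11% | 6% | 1% |
| Low group when 80% are high at baseline | 51% | 27% | 15% | 5% |

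The four-cell rows assume that potassium splits evenly and independently of awareness. In a cell of exactly 10, Fisher again needs five switches and rejects in 3% of trials at a 20% switch rate and 8% at 25%.

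**Step 4: five levels instead of low/high.** With equal level shares and the top two levels counted as high, a chi-square test on five levels rejects in 49% down to 8% of trials in the low group as r goes from 0.5 to 0.9. For at least one of the two groups the range is 77% down to 20%. Here 13–21% of low-group patients fall further despite no effect, across the settings run, so the movement is an average drift.

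**Step 5: does pairing rescue the subgroup test?** No. On low/high, every discordant pair in a subgroup points the same way, so six switches give an exact McNemar p of 2 × 0.5⁶ = 0.031. On five levels (cuts at 15/35/60/85%, low = levels 1–3), a Wilcoxon signed-rank test in the low group rejects in 46/27/18/12%.

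**Step 6: the same no-effect data, unsplit.** In the whole group, Fisher on low/high rejects in 0.0–0.7% and chi-square on five levels in 0.6–3.0%. The excess in the subgroups therefore comes from the split. The whole-group rates lie below 5% because these tests treat paired answers as independent. A whole-group Wilcoxon signed-rank test holds about 4–5%.

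**The case against.** The strongest reply is that the result depends on several readings of one sentence.

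- **Time point.** Enrolment is attached in words to potassium only. This stands as a point of wording. It does not rescue the test, because splitting on Questionnaire 2 would condition on the other half of the same change.
- **Item.** Questionnaire 1 has four items, and Q4 asks about burden rather than awareness. If one item forms the split and another is tested, the 0% and 100% starting points do not follow and the bias is weaker. This stands.
- **Cells.** The sentence can be read as crossing potassium with awareness, giving four cells of about 10. This stands and lowers the rates substantially (step 3).
- **Item and cut-off may be left to an analysis plan.** That is fair for those details. The instruction to repeat all of 3.5.2 in each subgroup is in the protocol, and a plan that follows it carries out the flawed test.
- **Low stakes.** The analysis is a subgroup analysis, awareness is called a secondary endpoint in 2.1, and section 20 calls the study exploratory. This bears on severity.

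A reader might infer that the low group can only rise and the high group can only fall. That is literally true only if the outcome is the same low/high split, which the protocol does not state. A reader might also infer that the test measures repeatability and nothing else. That goes too far, since a real effect would also lift the low group; the two are confounded.

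**Conclusion.** The concern holds in a limited form. On the natural reading, section 3.5.3 has change in awareness tested within groups selected on its own baseline value, without a control. The expected drift is one-directional by construction on a low/high outcome and an average tendency on five levels. The subgroup test cannot tell an effect of guidance from imperfect repeatability.

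For most of the assumed settings the false-positive rate exceeds the nominal 5%, often by a wide margin. Retest correlation, cut-off and cell structure are all assumptions. The excess is small or absent at high repeatability (5% for the four-cell and 80%-high cases at r = 0.9), and in a cell of about 10 when few patients switch by chance. The documents therefore do not support a claim that a false result is near certain.

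Severity is modest: the text should be changed, but the main analysis of serum potassium does not depend on it.

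**What to change.** 1. In 3.5.3, exclude the awareness-change test from the awareness-defined subgroups. Keep that split for serum potassium and blood pressure only.
2. In 3.5.2, test change in awareness in the whole Full Analysis Set with a paired method suited to five-level answers, for example the Wilcoxon signed-rank test, or McNemar's test if answers are collapsed to low/high. Moving the present Fisher or chi-square test to the whole group is not enough, because it ignores the pairing.
3. If dependence on starting awareness is of interest, show the Questionnaire 1 by Questionnaire 2 cross-table for each of Q1 to Q4 without p-values. Add a note that movement towards the middle is expected without any effect.

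This takes a few sentences and no new data. The sponsor gives up the p-value for change in awareness within the low-awareness group. The whole-group test still has no control, so it can show that awareness changed but cannot by itself attribute the change to guidance.
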